#### Monitoring

To ensure proper conduct of the study and reliability of the results, clinical monitors will visit the trial centres.

For one patient at each trial centre, 100% source data verification will be carried out.

For some randomly chosen patients, source data from the questionnaires will be partially checked against the case report form data. For each patient, the presence of a written consent will be verified.

### Biases

To avoid potential biases, this study is planned as randomized trial. Blinding will not be attempted because it cannot be successfully implemented as X-rays must be taken. Since the hybrid implant is expected to bring benefits in comparison with the conventional one, it must be tested in comparison to this control group.

To avoid bias without blinding design, the following measures are planned:Different trial physicians will carry out the surgery and the questionnaire surveyDifferent trial physicians will carry out the questionnaire survey and the evaluation of the X-raysThe patient will be instructed not to give any details of his treatment to the trial physicianThe trial physicians will be trained to evaluate the X-raysIntraoperative photos will be provided to compare the surgical techniques (approach, size of decompression) and, if need be, a video of the surgery for standardisation and training purposes

### Adverse and serious adverse events

#### Adverse event

An Adverse Event is any untoward medical occurrence in a study patient that may or may not have a causal relationship with the study treatment. Abnormal laboratory test values will be recorded as AE only if they require treatment.

##### Concomitant diseases

In this context, deterioration of a pre-existing disease is also to be regarded as an Adverse Event. But it will not be regarded as an Adverse Event if it is due to a treatment that was already planned before the patient was enrolled in the study.

##### Pregnancy

In this study, the occurrence of pregnancy is considered as an Adverse Event. Before surgery, laboratory tests will be conducted to exclude pregnancy in women below 50 years of age.

##### Laboratory test values

Any abnormal laboratory test values during the study will be checked for plausibility and evaluated for clinical relevance by the responsible investigator. If during the study, an abnormal test value is found that, in the baseline visit, was not considered to be clinically relevant, but is now considered to be clinically relevant, it must be recorded as an AE in the eCRF.

### Serious adverse event

The present clinical study is not subject to the Sections 20-23a of the German Medical Product Law (Medizinproduktgesetz – MPG), but its definitions will apply here. A Serious Adverse Event is any untoward occurrence in a clinical trial or in a performance evaluation text subject to approval that

directly or indirectly leads to death; orhave led, could have led, or could lead to a serious deterioration in the state of health of a study subject, of a user or of another person, irrespective of whether the occurrence has been caused by the medical product.

This definition of a SAE will serve as basis for the documentation of Serious Adverse Events during the study.

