#### Secondary target variables

All secondary target variables, such as frequency, average and standard deviation will be tabulated per point of time (baseline, 6 weeks, 6 months) and per treatment arm. The historical data for ODI, MCS of SF-36 of PCS of SF-36 will be expressed as AUCs (areas under the curve) adjusted for the observation period. Once the data have been collected after 6 weeks, 6 months and 36 months, the missing values, if any, will be interpolated after 12 or 24 months, or the AUC will not be evaluated. The two-sided t-test for independent samples will be used to compare the intervention group with the control group. The Logrank test will be used to compare the treatment groups in terms of survival time to instability measured by the Kaplan-Meier method. The link between time to instability and the ODI will be investigated by correlation analysis. Following evaluation of the primary endpoint, the ITT population and the PP population – as sensibility analysis – will be analysed.

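### The SAE definition mixes realised harm, merely possible harm and events in non-patients, so the by-arm SAE count does not measure serious harm to patients alone (minor)

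*Protocol article*

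**What the plan says.** All references are to the protocol article.

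- *Serious adverse event*: the study lies outside the named sections of the German device law, "but its definitions will apply here". Besides death and deterioration that did occur, an SAE includes an occurrence that "could have led, or could lead to a serious deterioration in the state of health of a study subject, of a user"; third persons are covered too, and it counts "irrespective of whether the occurrence has been caused by the medical product". The stated use is: "This definition of a SAE will serve as basis for the documentation of Serious Adverse Events during the study".
- *Adverse event*: "An Adverse Event is any untoward medical occurrence in a study patient", with or without a causal link to treatment.
- *Ascertainment of AE and SAE*: events are found by asking patients at each visit and by reviewing their records. For each AE the form takes dates, gravity, relationship to therapy, whether serious and whether expected.
- *Secondary outcome measures*: AEs and SAEs are on the list. So are mortality and, as a separate item, the complication rate including implant failure.
- *Secondary target variables*: all secondary variables "will be tabulated per point of time (baseline, 6 weeks, 6 months) and per treatment arm". No test specific to SAEs is named.
- *Interventions* and Appendix, *Safety*: the hybrid arm adds a flexible pedicle screw system above the fusion. Dynamic rod breakage is one of four listed kinds of implant failure.

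**The concern.** A definition built for device vigilance is meant to catch near misses and hazards to anyone. That suits documentation, but it is wider than what a by-arm harm table is usually read to show. The article's stated aim is to weigh benefits and harms to patients, and it gives only one SAE definition, so the tabulated outcome inherits it.

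Two things follow. First, the SAE category is wider than the AE category that should contain it. Second, realised and merely possible harm fall into one count. Whether something could lead to deterioration is a judgement, and the trial is unblinded. Exposure to hardware also differs by arm: there is more of it in the hybrid arm, and dynamic rod breakage can occur only there. Scheduled X-rays and checks for screw loosening and implant failure at follow-up visits could bring symptom-free findings to light. If those were classed as SAEs, the arms could differ without a difference in harm suffered. With about 20 patients per arm, each reclassified patient moves an arm's rate by 1/20 = 5 percentage points.

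**Working it through.** **1. The definitions side by side**

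| | AE definition | Ascertainment section | SAE definition |
|---|---|---|---|
| Who | study patient | patients asked, patient records reviewed | study subject, user or another person |
| What | an untoward medical occurrence | an AE, marked serious or not | harm that occurred, could have occurred or could occur |

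The first two columns make an SAE a serious AE in a patient. The third does not. The listed recording items contain no field that separates occurred from only possible, or patient from other person. Gravity might help in part, but nothing says that it is meant to.

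**2. Denominator**

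The article gives no SAE rate and no SAE power, so there is no SAE figure to reproduce. Its sample size supplies the denominator. With difference 11, SD 11.3, two-sided 5% and 80% power, the t-test calculation gives 17.58, so 18 per arm and 36 in total (power 81.0% at 18). Then 36/0.90 = 40, or 20 per arm. The stated figures reproduce.

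**3. How large could a tilt be?**

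Everything here is assumed except the 20 per arm and the 22% in (b). Let *b* be the rate of actual serious harm, equal in both arms.

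(a) *Silent screw findings, all counted as SAEs.* Assume 4 screws in controls, 6 in hybrid patients, and an independent probability *q* per screw. The SAE rate is 1 − (1 − b)(1 − q)^k, with k = 4 or 6. For b = 0.10 and q = 0.02:
- control: 1 − 0.90 × 0.98^4 = 0.170
- hybrid: 1 − 0.90 × 0.98^6 = 0.203
- excess: 0.033, or 0.66 patients of 20
- SE of the difference: √(0.170 × 0.830/20 + 0.203 × 0.797/20) = 0.123

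Excess in percentage points:

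| q | b = 5% | b = 10% | b = 20% |
|---|---|---|---|
| 0% | 0 | 0 | 0 |
| 1% | 1.8 | 1.7 | 1.5 |
| 2% | 3.5 | 3.3 | 2.9 |
| 5% | 7.5 | 7.1 | 6.4 |

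The largest excess is about 1.5 patients of 20. The SE of the difference runs from about 7 to 15 points across these cells.

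(b) *Silent findings in the dynamic rod only, rate r, all counted as SAEs.* The hybrid rate is 1 − (1 − b)(1 − r), so the excess is (1 − b)r. For r = 2% to 10% and b = 5% to 20%, it runs from 0.80 × 0.02 = 1.6 points to 0.95 × 0.10 = 9.5 points. Inserting the 22% hardware failure that the *Background* cites for another dynamic system, with b = 10%, gives 0.90 × 0.22 = 19.8 points. That is a worst case: it treats every failure in a different system as silent and as an SAE.

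(c) *Silent findings not classed as SAEs.* The excess is 0 and the ratio is 1.0. The text allows this as readily as (a) or (b).

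**The case against.** The strongest case against is that this is not a drafting slip. The device-law definition was adopted knowingly, and its stated use is documentation. How events are split in a table is commonly left to a full protocol or analysis plan, neither of which is shown. That stands against calling the definition wrong. It does not remove the mismatch with the AE definition, nor the fact that the recording items listed would not by themselves support a split later. The full eCRF is not shown and may already hold such an item.

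Four stronger readings are tempting, and the document does not support them:

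- *The SAE count fails to measure serious harm to patients.* Too strong: every death and every actual serious deterioration in a patient is still captured.
- *People outside the randomised denominator will enter the numerator.* Largely theoretical: events are found through patients and their records, and no route for user or third-party events is described.
- *The comparison is tilted by silent device findings.* Not shown: no text classes a symptom-free finding as an SAE, and the same definition applies to both arms.
- *The study question on complications cannot be answered.* It can: that question asks about the complication rate, with implant failure as its example, and this has its own outcome.

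It is also fair to say that a broken dynamic rod is a real consequence of the allocated treatment. It belongs in the results, but as implant failure; it is serious patient harm only if harm followed.

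**Conclusion.** The concern holds in a limited form. The article's SAE definition disagrees with its AE definition and its ascertainment section on who and what is counted. The by-arm SAE count built on it does not measure serious harm to patients alone. A difference between arms through possible-harm events is conceivable, because the hybrid arm carries more hardware, but it is not demonstrated. Its size is unknown: zero if silent findings are not classed as SAEs, and up to about 7.5 points (screws) or 9.5 points (dynamic rod) if all are, under the assumed rates above. For the screw scenarios this is small beside a standard error of about 7 to 15 points, although one or two reclassified patients would still visibly change a table of 20 per arm. Severity is minor. The primary ODI analysis and the sample size are unaffected.

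**What to change.** 1. Keep the current SAE definition for documentation and reporting, and add a sentence reconciling it with the AE definition, which covers only "any untoward medical occurrence in a study patient".
2. In the by-arm SAE table, count randomised patients with at least one event that actually led to death or serious deterioration.
3. List possible-harm events, and any events in users or other persons, separately.
4. Add one eCRF item to those in *Ascertainment of AE and SAE*: occurred or only possible; patient or other person. If the full eCRF already has it, only the table split is needed.

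The cost is one form item and one split table; reporting duties do not change. The main SAE comparison will contain fewer events. The new item would still be completed open-label, so it makes the judgement visible but does not remove it.

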### Ascertainment of AE and SAE

The study centre concerned is responsible for recording and reporting AEs and SAEs. The study director/main investigator will ensure that all persons involved in the treatment of the study patients are fully aware of their responsibilities in the event of Adverse Events. At each visit, the patients will be asked if they have experienced any Adverse/Serious Events. The Adverse Events will be recorded both in the patients’ medical record and in the survey questionnaires. At each visit, the physician will review the patients’ medical records to determine whether Adverse Events have occurred.

If an Adverse Event occurs, the patient in question, irrespective of the causal relationship between the Adverse Event and the study treatment, must be kept under constant supervision. In any case, the patient must remain under observation until the symptoms have subsided, or the laboratory test values have returned to acceptable levels, or a plausible explanation has been found for the Adverse Event, or until the patient has died, or has been discharged from the study (last visit after 6 months or 36 months).

All Adverse Events will be recorded in the CFR, including the following information:

Time and date of start and end ,Gravity ,Relationship to the study therapySerious or not serious ,Expected or not expected ,

## Discussion

New “topping off” hybrid systems might reduce the complications associated with lumbar spine fusion. But to date, there is no convincing evidence to confirm this hypothesis. This study is intended to fill this gap by providing highly reliable data and a preliminary evaluation of the advantages and disadvantages of a device that was launched in 2013. These systems are much more expensive than conventional implants, they should not be implanted if they do not bring any appreciable benefit, an aspect which is of interest to the health care providers. This study is designed as a randomized clinical trial, a format highly recommended to evaluate the benefits and risks to patients of new devices.

In the intervention group, the approach to the spine will be larger than in the fusion group. This in itself could bring about a negative outcome compared to that of standard fusion (e.g., due to muscle damage, blood loss, higher risk of infection). But implant failure rates can still be compared between the groups. The crucial question, however, is the ability to prevent ASD.

To use a placebo in the control group would be fundamentally unethical. Not only would it deprive the patient of adequate treatment, but would also require an invasive procedure without implantation, thus exposing him/her to significant risks without benefit. Furthermore, there is no “placebo device” that could be used here.

## Appendix

### Inclusion criteria

Informed consentLegal capacityAge ≥ 30 yearsIndication for monosegmental lumbar spine fusion L2-S1 with osteochondrosis Modic grades I-IIIIndication for monosegmental lumbar spine fusion L2-S1 with spondylolisthesis Meyerding grades I-III (signs of instability in the functional x-rays and a.p. and lateral view; see definition of radiologic instability).Indication for monosegmental lumbar spine fusion L2-S1 with symptomatic facet joint arthrosis or degenerative disc disease (>Fujiwara grade II [23] or > Pfirrmann grade IV [22])Radiologic signs of degeneration in the adjacent segment of the intended fusion without signs of instabilityDefinition of adjacent segment degeneration (MRI)Pfirrmann [22] grades II-IVGrade I: Homogeneous bright white structureGrade II: Inhomogeneous white structure, possible horizontal bandsGrade III: Clear distinction between annulus and nucleusGrade IV: Non-collapsed disk spaceGrade V: Collapsed disk spaceDefinition of radiologic instability (x-ray: a.p. and lateral view, extension and flexion):Spondylolisthesis >4 mm (anterior or posterior translation) [3]Segmental kyphosis >10° [3]Rotatory hypermobility >15° [14]Complete collapse of the disc [3]Lateral translation >3 mm [14]Disc wedging >5° [14]Deterioration in Weiner’s classification of 2 or more grades in the follow-up evaluation [1, 27]

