### Participants and recruitment

Outpatients over 30 years of age presenting with degenerative disc disease, facet joint arthrosis or spondylolisthesis, and indications for monosegmental lumbar spine fusion will be eligible for trial inclusion. Radiologic inclusion criteria are summarized in the Appendix.

The presence of radiologic degeneration of the adjacent segment (Pfirrmann grades II-IV in MRI findings [22]) without signs of instability will be a condition for inclusion. The definition of radiologic and clinical instability and the other inclusion criteria are summarized in the Appendix.

Experienced spine surgeons will approach and recruit the study subjects. The number of patients who undergo primary monosegmental fusion in the departments is estimated at 200 per year and the number of recruited patients at 20 per year per centre.

Patients participating in parallel interventional studies as well as patients with lumbar scoliosis (>25° cobb angle), spondylolisthesis Meyerding IV, adjacent segment instability and/or radiologic ASD worse than Fujiwara grade II or Pfirrmann grade IV [22, 23] will be excluded from this study. This also applies to patients with indication for multilevel fusion. The other exclusion criteria are summarized in the Appendix.

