### Secondary outcome measures

PCS of the SF-36™. The SF-36™ is the most frequently used generic health status measure worldwide that includes parameters such as pain and walking distance. It has been further developed to comprise physical (PCS) and mental health (MCS) component scores, thus easing the interpretation and cross-cultural comparison. It is a standardized questionnaire used to evaluate the patients’ health-related quality of life. It yields an 8-scale profile of functional health and well-being scores, as well as psychometrically based physical and mental health summary measures, and a preference-based health utility index. Thus, the SF-36™ is a good measure of primary endpoint. The patients' answers are scored and added together to yield a sum total. The SF-36™ PCS scores of the experimental and control groups will be compared to further quantify patient outcomes. In the subsequent follow-ups, the SF-36™ will be repeated to detect any clinical impairment and/or clinical or radiologic instability. This follow-up will continue for up to 3 years and then each year after surgery. In cases of impairment, X-ray is indicated at any point of time. In total, MCS and 8 individual dimensions and subscales of the SF-36™ (version 4.0) are used to confirm and clarify the primary outcome results.COMI questionnaire (2008 version) - a short, patient-oriented, multidimensional outcome instrument validated for patients with spinal disorders.X-rays will be taken after 6 weeks, and after 6, 12, 24, and 36 months. A further assessment will be performed every year. These are common intervals after surgical implantation without extraneous radiation. If adjacent instability is discovered on a X-ray, the clinical outcome will be reevaluated. The criteria for both radiologic ASD and adjacent instability are listed in the Appendix (definition of radiologic instability and Weiner’s classification). Experienced radiologists will evaluate the pre- and postoperative X-rays to calculate the score in Weiner’s classification. Furthermore, after 6 months, full-length X-rays of the spine will be taken to assess sagittal balance parameters (pelvic incidence, sacral slope, pelvic tilt, lumbar lordosis, C7 plum line, SVA). At each follow-up visit, bone fusion will be evaluated by indirect signs (screw loosening, implant failure, loss of reduction).Clinical ASD will be assessed (see definition in the Appendix).Work disability at the time of and after surgery, and duration until return to work. At each visit, patients will be asked to grade their disability, and whether or when they have returned to work.Inpatient mortality and mortality at 6 months.Surgery-related data (blood loss, length of incision, duration of surgery) will be taken from the surgical report.During the study, type and dose of pain medication administered to the patients will be documented. If the patient complaints of pain, the medication will be adjusted. The adjustment will be recorded on the CRF.Intraoperative and postoperative complication rate (e.g. implant failure- see Appendix under “Safety”)Adverse Events (AE) and Serious Sdverse Svents (SAE) will be monitored and documented throughout the study (see Appendix under “Safety” and “AE and SAE”).

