### Weiner’s classification

0 = No disease, defined by normal disc height, no spur formation, no eburnation, and no gas

1 = Mild disease, defined by <25% disc space narrowing, small spur formation, minimal eburnation, and no gas

2 = Moderate disease, defined by 25%-75% disc space narrowing, moderate spur formation, moderate eburnation, and no gas

3 = advanced disease, defined by >75% disc space narrowing, large spur formation, marked eburnation, gas present

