### Exclusion criteria

Motor deficitCauda equina syndromePrevious surgical intervention of the lumbar spineRelevant peripheral neuropathyAcute denervation subsequent to radiculopathyScoliosis with Cobb angle greater than 25°Spondylolisthesis > Meyerding grade IIIRadiologic signs of degeneration in the adjacent segment of the intended fusion with signs of instability (for definition, see inclusion criteria)No radiologic signs of degeneration in the adjacent segment of the intended fusion (for definition, see inclusion criteria)Radiologic signs of degeneration in the adjacent segment of the intended fusion with > Fujiwara grade II [23] or > Pfirrmann grade IV [22]Signs of instability in any lumbar spine segment other than that undergoing fusion (patients with indication for multilevel fusion are excluded)General contraindication for elective lumbar spine surgeryPathologic fractureOsteoporosis with pathologic fractureActive systemic infectionRheumatic diseaseDisease of bone metabolism (e.g. Paget’s Disease)Bone metastasisLocal infection of lumbar spineSeizure disorderChronic ischemia according to Fontaine classification IIb-IVSevere heart insufficiency (NYHA III-IV)Blood coagulation disorder or blood thinning therapyCortisone intake more than one month in the last 12 months before randomizationSimultaneous participation in another clinical trial in the 30 days before randomizationKnown allergy or intolerance to the implantsDependency on investigatorLack of familiarity with the German languagePlacement in an institution by governmental or juridical orderAbsent legal capacityPregnancyLactation period

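### One of the seven radiologic instability criteria, a Weiner worsening of 2 or more grades on a 0-3 scale, is out of reach for patients who start at grade 2 or 3, so progression from 2 to 3 goes uncounted

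*Protocol article*

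**What the plan says.** The definition of radiologic instability stands under Inclusion criteria in the protocol's appendix. It lists seven items: anterior or posterior translation, segmental kyphosis, rotatory hypermobility, complete disc collapse, lateral translation, disc wedging and, last, "Deterioration in Weiner’s classification of 2 or more grades in the follow-up evaluation".

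The appendix section on Weiner's classification gives four grades. The lowest is "0 = No disease, defined by normal disc height, no spur formation, no eburnation, and no gas". The two highest begin "2 = Moderate disease, defined by 25%-75% disc space narrowing" and "3 = advanced disease, defined by >75% disc space narrowing".

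On entry, Participants and recruitment makes the following, in a stable segment, a requirement for enrolment: "The presence of radiologic degeneration of the adjacent segment (Pfirrmann grades II-IV in MRI findings [22"]). The exclusion list mirrors this with "No radiologic signs of degeneration in the adjacent segment of the intended fusion (for definition, see inclusion criteria"). The upper limits at entry are expressed in Fujiwara and Pfirrmann grades and as absence of instability. None is expressed in Weiner grades.

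On use as an outcome, Secondary outcome measures says: "The criteria for both radiologic ASD and adjacent instability are listed in the Appendix (definition of radiologic instability and Weiner’s classification"). Radiologists score the pre- and postoperative films on Weiner's scale. Under Secondary target variables, time to instability is compared between arms by Kaplan-Meier and log-rank, and its link with the ODI is studied by correlation.

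**The concern.** The trial selects patients whose adjacent segment is already degenerated. One of its progression criteria, however, needs two free grades above the starting point on a four-grade scale. Patients at the more degenerated end of the Weiner scale have no such room.

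The item also orders severity unevenly. A change from 0 to 2 counts, although the patient ends with moderate disease. A change from 2 to 3 does not, although the end state is worse. Two patients who both finish at grade 3 are classified differently if one began at 1 and the other at 2.

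At stake is the Objective's question whether the device prevents adjacent instability or segment disease, and its question whether radiographic ASD correlates with clinical outcome. The Discussion calls the ability to prevent ASD the crucial issue. An outcome that misses some true progression has fewer events, and the patients concerned enter the correlation analysis as event-free when their segment has in fact worsened.

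**Working it through.** **Figures the plan states.** The protocol gives no event rate, event count or sample size for instability, so there is nothing of that kind to reproduce. The only denominator is the ODI sample size. With SD 11.3, difference 11, two-sided 5% and 80% power, the two-sample t-test needs 17.58, so 18 per group and 36 in total. With 10% drop-out, 36 / 0.90 = 40. This agrees with the protocol and serves below only as the denominator.

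**Ceiling check.** Maximum possible worsening = 3 − preoperative grade. The item requires at least 2.

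| Preoperative Weiner grade | Maximum worsening | Follow-up grades that meet the item |
|---|---|---|
| 0 | 3 | 2 or 3 |
| 1 | 2 | 3 only |
| 2 | 1 | none |
| 3 | 0 | none |

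**Can such patients be enrolled?** The appendix describes Pfirrmann grade IV, the highest allowed, as a disc space that has not collapsed. A disc narrowed by 25% to 75% is Weiner 2 and has not collapsed, so nothing in the entry criteria shuts it out. Entry at Weiner 3 is less clear: the document does not say at what narrowing a disc counts as collapsed, and collapsed discs are excluded. Grade 2 is therefore the clear case.

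**What the other six criteria catch.** Five concern motion or alignment. The sixth is complete disc collapse. A grade 2 patient who reaches grade 3 (more than 75% narrowing, with gas) without complete collapse, and without crossing a motion or alignment threshold, has no event.

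**How many patients?** The document gives no share at grade 2 or 3, so the whole range is shown as an assumption. Patients unable to meet the item = 40 × share.

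| Assumed share at grade 2 or 3 | Cannot meet the Weiner item | Can meet it |
|---|---|---|
| 0% | 0 | 40 |
| 25% | 10 | 30 |
| 50% | 20 | 20 |
| 75% | 30 | 10 |
| 100% | 40 | 0 |

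Nothing in the document favours one row over another.

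**The case against.** Four points can be made on the other side.

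First, a reader might infer that patients starting at grade 2 or 3 can never have a radiologic event. The text does not support that. Weiner deterioration is one of seven items. On the natural reading any one suffices, and the other six can be reached from either grade. This stands, and it confines the point to the Weiner item.

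Second, a reader might infer that requiring degeneration fills the trial with patients at the ceiling. That does not follow either. Entry is graded on MRI, where Pfirrmann II and III are described by disc structure and not by height. Weiner is graded on X-ray by narrowing, spurs, eburnation and gas. Many enrolled patients may start at Weiner 0 or 1, and the exclusions for collapse, instability and Fujiwara above II limit severe disease at baseline. This stands, and it leaves the number affected unknown.

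Third, the list defines instability and not every step of degeneration. A two-grade threshold, which the protocol supports with citations, may be deliberately strict. It also resists reading error: on narrowing alone, going from 74% to 76% crosses a grade boundary while going from 26% to 74% crosses none. In an unblinded trial this is a good reason not to put one-grade steps into the main definition. It does not remove the ceiling, and Secondary outcome measures applies the same list to radiologic ASD as well as to instability.

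Fourth, Weiner grades are scored in any case, and secondary variables are to be tabulated by arm, including at baseline. That covers part of the remedy, but the tabulation names only baseline, 6 weeks and 6 months, and the stated test is the log-rank on the present event definition.

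**Conclusion.** The point holds for the Weiner item alone. That item cannot be met from preoperative grade 2 or 3, and from grade 1 only by reaching the top grade. As a result, worsening from grade 2 to 3 short of complete collapse is not counted in the secondary time-to-instability and radiologic ASD outcomes unless another criterion is also met. The ceiling follows from the appendix alone and needs no assumption. That the other criteria remain open rests on reading the list as any one of seven, which the text does not spell out.

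The size cannot be stated. It depends on the preoperative Weiner distribution, which is not given, and could be anything from none of the 40 patients to a substantial part of them.

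It would be too strong to conclude that the trial's main result is at risk, or that the definition must be replaced. The primary ODI comparison at 6 months and its sample size do not depend on this definition, and clinical ASD is assessed separately. The consequence is a loss of sensitivity in one component of a secondary outcome, and added analyses can make good much of it.

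**What to change.** Keep the stated definition for the main log-rank analysis, and add two items to the analysis of secondary target variables.

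(a) Report the preoperative Weiner grade of the adjacent segment by arm. At each X-ray visit (6 weeks, then 6, 12, 24 and 36 months), compare follow-up Weiner grade between arms as an ordinal outcome adjusted for the preoperative grade.

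(b) Run a sensitivity time-to-event analysis in which progression from grade 2 to grade 3 also counts as an event. State that patients at preoperative grade 3 are judged on the other six criteria only.

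The cost is a little more analysis and one extra table. No visit, film, reader or entry criterion changes, because the pre- and postoperative films are already scored. The drawback is that a one-grade step is more open to reading error, which is why it belongs in the sensitivity analysis and not in the main definition. With 40 patients some grades will be sparse, so the ordinal result should be presented as supportive.
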